### Basic characteristic variables

Collected baseline data include the following:Demographic characteristics, such as sex, age, ethnicity.Biochemical and clinical measurements, such as routine blood, stool, and urine tests; tests for hepatic and renal functions; ion tests; electrocardiography (ECG); and measurement of ascites depth, abdominal perimeter, body weight, and urine output.Main symptoms, such as abdominal distension, appetite, level of exhaustion, and normal/abnormal defecation.Health-related quality-of-life scale for patients with chronic liver disease.Disease course, combined drugs, and other relevant information.

Vital signs, including blood pressure, pulse, respiratory rate, and body temperature, will also be recorded every day.

### Primary outcomes

The primary outcome measurement will be the depth of ascites. It will be measured at baseline using B-ultrasound, after the intervention (10 days), and at the end of the 30-day follow-up period.

### Secondary outcomes

Secondary outcome measurements include the abdominal perimeter, body weight, the 24-h urine volume, the symptomatic score of TCM, and the CLDQ, which will be measured at baseline, after the intervention (10 days), and at the end of the 30-day follow-up period. The abdominal perimeter, weight, and 24-h urine volume will be measured every day from the baseline to the end of the 30-day follow-up period. The symptomatic score of TCM contains the patient’s primary symptoms, such as abdominal distension, appetite, level of exhaustion, normal/abnormal defecation, and so on. The CLDQ is a disease-specific tool designed to assess health-related quality of life in patients with chronic liver disease [15].

### Safety assessment

Primary vital signs, physical examinations, and some laboratory tests will be performed both before and after treatment for safety assessment daily. Primary vital signs include body temperature, blood pressure, heart rate, and respiratory rate. Laboratory tests include routine blood, urine and stool tests, along with fecal occult blood tests; ECG; liver function tests (alanine aminotransferase (ALT), aspartate aminotransferase (AST), alkaline phosphatase (ALP), gamma-glutamyl transpeptidase (GGT), and serum total bilirubin (TBIL)); renal function test (serum creatinine (Cr) and blood urine nitrogen (BUN)); and electrolyte test (K^+^, Na^+^, Cl^−^, and Ca^2+^).

### Adverse events

All unexpected AEs occurring during the intervention period will be reported, and the causality related to the LSXG cataplasm will be analyzed. If any adverse event occurs, the study managers will ensure that the participant receives adequate treatment. The AEs will be immediately reported to the principal investigator and to the ethics committee to decide whether the participant should withdraw from the trial. If any symptoms aggravate, the patient will be withdrawn from the study and will be referred for further treatment.

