## Background

Liver cirrhosis is a diffuse hepatic process, characterized by fibrosis and structurally abnormal nodules, representing the final histological change due to various chronic liver diseases [1]. Ascites is the most common complication of decompensated cirrhosis, which is often associated with a poor prognosis and impaired quality of life. Mortality among patients with cirrhotic ascites is approximately 40% at 1 year and 44–85% at 5 years [2, 3]. In the absence of proper treatment, large ascites may lead to dyspnea, umbilical hernia, acid–base disturbances, hepatic encephalopathy, hepatorenal syndrome, and even death.

In recent years, a series of clinical practice guidelines regarding the management of ascites has been published [4–6], providing recommendations for ascites treatment including diuretic therapy, large-volume paracentesis, and albumin infusion. However, some limitations remain, particularly concerning the side-effects of the standard treatment for refractory ascites. Therefore, it is crucial to find better practices to successfully manage ascites.

Traditional Chinese medicine (TCM), including internal and external therapeutic approaches, has been used to treat ascites for over 1000 years. According to the meridian–collateral and visceral theories of TCM, the application of herbal remedies to the umbilical region, covered and fixed with a medical gauze and adhesive tapes, along with hot ironing, can play an important role in the treatment of various diseases, including cirrhotic ascites [7]. Previous studies have reported the use of umbilical therapy to treat ascites [8, 9]. However, they lacked a rigorous trial design. Moreover, a previous study performed by our group has demonstrated a significant effect of *Lishui Xiaogu* (LSXG) cataplasm treatment for ascites. Therefore, we designed the present randomized controlled trial (RCT), which obtained special support from the Beijing Capital Characteristic Clinical Application Research Project by the Beijing Municipal Science & Technology Commission of China. Our aim is to evaluate the efficacy and safety of the LSXG cataplasm umbilical therapy in patients with cirrhotic ascites, using a rigorous prospective randomized controlled clinical trial. The findings of this trial may establish the corresponding operational criteria and obtain evidence-based medical evidence, so as to provide an effective alternative measure for the treatment of cirrhosis ascites.

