### Interventions

Patients in the LSXG group will receive the umbilical therapy with LSXG cataplasm plus red light irradiation along with conventional treatment, whereas patients in the placebo group will receive the placebo cataplasm plus red light irradiation along with conventional treatment. The treatment will be administered once daily for up to 10 days, with a 30-day follow-up after the last treatment.

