For cataplasm application: the umbilical region should be thoroughly cleaned with an iodophor solution; the patients must be rested and abstain from stimulating food, such as pungent food, seafood, or raw and cold food, and the cataplasm should not be applied immediately before a meal; the amount of formula administered and the time of administration should be adjusted for weaker patients (any changes in patient conditions should be recorded); if the cataplasm application triggers erythema, blisters, or itching, it should be removed; and the cataplasm should be contraindicated in patients with known allergies to any of the constituents, pregnant patients, and patients presenting with edema with Yin-shui syndrome. This application should be used with caution in weaker patients.

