## Discussion

Umbilical therapy with TCM formulations has a long history in China, and has been popularly used to treat various diseases, including cirrhotic ascites. Through being applied to the umbilical region, TCM may be absorbed into the blood quickly and stimulate peripheral nerves, which may be the reason for its action. Also, as a complementary therapy, it is easy to operate and convenient, compared with acupuncture, moxibustion, and TCM soups.

Previous studies preliminarily showed that umbilical therapy is effective and safe in treating cirrhotic ascites [8, 9, 16–19]. One meta-analysis demonstrated that umbilical therapy was more effective in increasing 24-h urinary volume, decreasing patients’ weight and abdominal circumference, compared with conventional medicines. Adverse reactions were rarely reported, which often include skin itching or partial flushing due to the adhesive plaster [8]. Another meta-analysis of mirabilite umbilical compress in treatment of ascites in liver cirrhosis showed similar results [9]. Application of Shehuang Paste to the umbilical area was also reported to reduce blood flow of the portal vein and the splenic vein, and to lower the content of endotoxin, nitric oxide, and endothelin-1 [8].

However, the lack of high-quality evidences limits the application of umbilical therapy [8]. Most studies were small sample, unblind, and based on one medical center, which may lead to bias caused by confounding factors. Besides, some studies took the 24-h urinary volume, patients’ weight, and abdominal circumference change as primary outcomes, which could not reflect the dynamic change of ascites directly [18, 20]. Based on previous research [14], our study will be the first central-randomized, double-blind, parallel, placebo-controlled, multicenter trial, using the dynamic change of ascites by B-ultrasound as the primary outcome. In conclusion, we present the protocol of a randomized controlled, double-blind, multicenter trial, aiming at evaluating the efficacy and safety of umbilical therapy for cirrhotic ascites, as a complementary and alternative therapy. Results of the current study will provide high-quality evidence supporting the management of ascites using umbilical therapy with TCM.

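### The sentence that sets the scope of adverse event reporting is, read literally, too narrow for a joint safety aim, and it conflicts with other text in the protocol

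*Protocol article*

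**What the plan says.** The protocol article gives safety the same standing as efficacy. Its Background section states: "Our aim is to evaluate the efficacy and safety of the LSXG cataplasm umbilical therapy in patients with cirrhotic ascites".

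The Adverse events section then opens with the reporting rule: "All unexpected AEs occurring during the intervention period will be reported, and the causality related to the LSXG cataplasm will be analyzed". The next sentence of that section is wider: "If any adverse event occurs, the study managers will ensure that the participant receives adequate treatment". The one after it sends AEs to the principal investigator and the ethics committee at once, without restricting them by expectedness or date.

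The length of the intervention period comes from the Interventions section: "The treatment will be administered once daily for up to 10 days, with a 30-day follow-up after the last treatment".

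The protocol foresees local reactions. The Traditional Chinese medicine intervention section says: "if the cataplasm application triggers erythema, blisters, or itching, it should be removed". On earlier studies of umbilical therapy, the Discussion says: "Adverse reactions were rarely reported, which often include skin itching or partial flushing due to the adhesive plaster".

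Safety examinations are set out in the Safety assessment section: "Primary vital signs, physical examinations, and some laboratory tests will be performed both before and after treatment for safety assessment daily". Follow-up is not mentioned there.

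**The concern.** The reporting sentence contains two qualifiers, and each removes something that a safety comparison would normally include.

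- **Expectedness.** If only unexpected events are reported, a foreseeable reaction need not be. Erythema, blisters and itching at the application site are foreseeable by the protocol's own account. The instruction attached to them is to take the cataplasm off; that sentence does not ask for the reaction to be recorded as an AE.
- **Window.** If only the intervention period counts, an AE that starts after the last application falls outside the rule, although participants stay on study for another 30 days and efficacy is measured throughout that time.

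At stake is how the safety result can be read. If the three centers applied the sentence literally, a low AE count would partly reflect the collection rule. If some applied it literally and others recorded everything, pooled AE counts would mix two definitions. The condensed format of a journal article does not account for this, because the article does state a scope.

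**Working it through.** The plan gives no figure on this point to reproduce. The check is a comparison of the text plus one line of arithmetic.

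**Length of the window**

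- Treatment: at most 10 days (Interventions).
- Follow-up after the last treatment: 30 days (Interventions).
- Time on study: 10 + 30 = about 40 days.
- Share inside the literal reporting window: 10 / 40 = 25% at most. A participant treated for fewer days has a smaller share.
- Share outside: 30 / 40 = 75%.

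These are shares of calendar time only.

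**What each section says about AE scope**

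| Section | Limited to unexpected events? | Limited in time? |
|---|---|---|
| Adverse events, first sentence | Yes | Yes, intervention period |
| Adverse events, later sentences | No | No |
| Abstract, Methods/design | No | No |
| Statistical analysis | No | No |
| Background (safety aim) | No | No |
| Safety assessment (examinations and tests) | No | Before and after treatment, daily; follow-up not mentioned |
| Study design and setting | Does not mention AEs | Places every assessment at baseline, end of treatment and end of follow-up, directly after a list of efficacy outcomes |

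**Reasoning**

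1. Only the first sentence of the Adverse events section defines a scope. The other sections mention AEs without saying which ones or until when. They therefore contradict the narrow rule but do not replace it with another.
2. The term *unexpected* is not defined in the article. On its ordinary meaning it excludes the three local reactions named in the Traditional Chinese medicine intervention section.
3. The Safety assessment section does not close the follow-up gap, because it ties its examinations to treatment. The three time points under Study design and setting could be read as including safety, but their position after the efficacy outcomes leaves this open.
4. Efficacy follow-up is longer than AE follow-up on the literal rule. Ascites depth is measured at the end of follow-up (Primary outcomes). Abdominal perimeter, weight and urine volume are measured daily until then (Secondary outcomes). Contact with participants therefore already exists in the period that the AE rule leaves out.
5. The same sentence ties causality to the LSXG cataplasm, while researchers are blinded (Randomization and allocation concealment). A blinded assessor does not know which preparation a participant received, so the question can be put in the same way in both arms only if it refers to the study cataplasm.

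**The case against.** The strongest reply is that one loosely worded sentence is being given too much weight. *Unexpected* may be a loose rendering of untoward. The safety aim is unrestricted, the Abstract and the Statistical analysis section refer to AEs without qualification, and the next sentences of the Adverse events section do the same. This stands in part: it shows that the authors may have intended, and may be practising, full collection. It does not remove the defect, because none of those places states a scope or an end date, and the sentence that does is narrow.

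A reader might go further and infer that the skin reactions and everything in follow-up lie outside the safety objective, or that all delayed harm will be missing. The documents do not support that. The Discontinuation section lists hemorrhage, encephalopathy and hepatorenal syndrome among its grounds and has reasons for discontinuation entered on case report forms. The Dropout section counts participants who fail to complete observation, whatever the time or reason, and names serious AEs and complications among the causes. Whether the case report form entry extends into follow-up is not stated either way. The examinations and laboratory tests under Safety assessment do not depend on whether an event was expected.

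Three further limits on the point are fair:

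- The 75% is time, not harm. Local reactions to a daily topical application would be expected mainly while it is being applied, inside the window.
- Flushing appears only in the account of earlier studies, where it and itching are put down to the adhesive plaster. It should not be added to the reactions that this protocol foresees for its cataplasm.
- Nothing in the sentence confines reporting to one arm, and blinded causality assessment largely follows from the blinding already described. On causality, the change needed is one of wording.

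That a trial of this size can exclude only fairly common harms is also true, but it would hold under a perfect AE rule and does not measure this defect.

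**Conclusion.** The point holds as an internal inconsistency and a badly fixed rule. The only sentence that defines AE reporting restricts it by expectedness and to at most 10 of about 40 days. Followed literally, it omits foreseeable erythema, blisters and itching, and any AE that starts in the 30-day follow-up. It conflicts with the unrestricted AE wording elsewhere in the article and with the joint safety aim.

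The size in events cannot be given, because the documents contain no AE rates by period and do not show what the centers have actually recorded. The effect is confined to the safety comparison; the efficacy analysis is untouched.

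The conclusion assumes that *unexpected* carries its ordinary meaning and that the schedule in Fig. 2, which was not available in the text, does not set a wider AE window. If the figure or the full protocol does so, what remains is a correction of wording. The point deserves action before unblinding, since at manuscript submission 78 of the planned 82 participants had been enrolled (82 − 78 = 4 remaining).

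**What to change.** **Text.** Amend the first sentence of the Adverse events section, and reconcile the Abstract, Study design and setting, Safety assessment and Statistical analysis with it, so that they state together:

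- all AEs, expected or unexpected, are recorded in both arms from first application to the end of the 30-day follow-up;
- causality is judged in relation to the study cataplasm, in the same way for every participant;
- AEs are reported by arm, with local skin reactions in a separate table and the treatment and follow-up periods shown apart;
- whether safety examinations and tests are done in follow-up and, if so, when.

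**Patients already enrolled.** Before unblinding, check at each center whether foreseeable reactions and follow-up events were recorded. Where they were not, complete them from existing source notes, and flag every event collected in this way so that the analysis can be shown with and without them.

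**Cost.** A wording amendment, which the Ethics section says must go to the Institutional Review Board, and a small amount of extra data work, since contact during follow-up already exists. The observed AE rate will be higher. Retrospective completion may under-record mild events, so those counts should be described as a lower bound.

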## Methods/design

### Study design and setting

This ongoing study was designed as a central-randomized, double-blind, parallel, placebo-controlled, multicenter trial. The study was designed using the Consolidated Standards of Reporting Trials (CONSORT) 2010 guidelines [10]. Also, we designed the trial based on the Standard Protocol Items: Recommendations for Interventional Trials (SPIRIT) statement. The study is being performed in three centers in China, namely: Dongzhimen Hospital, affiliated to Beijing University of Chinese Medicine; Beijing Tongzhou District Hospital of Traditional Chinese Medicine; and Beijing Pinggu Hospital of Traditional Chinese Medicine. Patients with cirrhotic ascites, who meet the inclusion criteria, will be allocated in a 1:1 ratio to either a LSXG group or a placebo group. Patients in the LSXG group will receive umbilical therapy with the LSXG cataplasm plus red light irradiation along with conventional treatment; patients in the placebo group will receive umbilical therapy with a placebo cataplasm plus red light irradiation along with conventional treatment. Based on clinical experience, the treatment will be administered once daily for up to 10 days, with a 30-day follow-up after the last treatment. The depth of ascites will be assessed as the primary outcome measurement. The abdominal perimeter, body weight, urine volume, the symptomatic score of TCM, and the Chronic Liver Disease Questionnaire (CLDQ) will be used as secondary outcome measurements. All assessments will be conducted at three time points: at baseline, after the last treatment, and after the 30-day follow-up period. The flow chart is shown in Fig. 1. We also provide the Standard Protocol Items: A Recommendations for Interventional Trials (SPIRIT) figure (Fig. 2) and the corresponding checklist (Additional file 1).

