### Informed consent

Prior to the study, the general study process and the responsibilities of the participants and researchers will be explained to potential participants. Participants will be informed that their entry into the trial is entirely voluntary and that they can withdraw at any time. In the event of their withdrawal, data collected on the participant will not be erased and will be used in the final analyses. Written informed consent will be obtained from each participant before they undergo any interventions related to the study.

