#### Discontinuation

Participants who meet any of the following exclusion criteria will be discontinued:Discontinuation of treatment.Occurrence of serious adverse events (AEs) related to the research medication.Occurrence of serious complications, such as gastrointestinal hemorrhage, spontaneous peritoneal inflammation, primary hepatic carcinoma, hepatic encephalopathy, and hepatorenal syndrome.Worsening of disease, which will require emergent treatment.Termination of the trial by the administrative authorities.

Reasons for discontinuation will be recorded on case report forms (CRFs), and the last data recorded for such participants will be included in the data analysis.

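### The Adverse events section orders withdrawal from the study if any symptom worsens; this conflicts with two other rules and can end measurement of ascites depth in patients who deteriorate

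*Protocol article*

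**What the plan says.** Four parts of the protocol article bear on a patient who gets worse.

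- **Adverse events, last sentence:** "If any symptoms aggravate, the patient will be withdrawn from the study and will be referred for further treatment". The sentence before it sends adverse events to the principal investigator and the ethics committee "to decide whether the participant should withdraw from the trial".
- **Discontinuation:** the criterion for worsening is "Worsening of disease, which will require emergent treatment". Other criteria are stopping treatment, serious related adverse events, serious complications and termination by the authorities. For patients discontinued under this section, "the last data recorded for such participants will be included in the data analysis".
- **Rejection:** one criterion rejects participants who stop treatment after baseline.
- **Informed consent:** after withdrawal, "data collected on the participant will not be erased and will be used in the final analyses".

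Ascites depth is the primary outcome, and Statistical analysis assigns it to intention-to-treat. On timing, Primary outcomes says: "It will be measured at baseline using B-ultrasound, after the intervention (10 days), and at the end of the 30-day follow-up period". Study design and setting says: "All assessments will be conducted at three time points: at baseline, after the last treatment, and after the 30-day follow-up period", with treatment given for at most 10 days. No section says that a withdrawn patient is still measured.

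**The concern.** The last sentence of Adverse events removes the patient from the study, not only from the cataplasm, and any degree of aggravation is enough. Secondary outcomes scores the patient's "primary symptoms, such as abdominal distension, appetite, level of exhaustion, normal/abnormal defecation", so on the literal wording a rise in distension alone would trigger exit. Distension is also part of the entry criteria.

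If sites follow the sentence, the patients whose 30-day depth goes unmeasured are those who worsened. Such loss can depend on the outcome. An analysis plan can choose how to handle missing values, but it cannot recover an ultrasound that was never taken. Intention-to-treat for the primary outcome then keeps patients in the count without the measurement it needs. Abdominal perimeter, weight and urine volume, scheduled daily to the end of follow-up, would stop at exit too.

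**Working it through.** **1. The three rules side by side, for a patient whose distension increases without need for emergent treatment**

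| Rule | Result |
|---|---|
| Adverse events, last sentence | Leaves the study automatically |
| Adverse events, sentence before (if reported as an adverse event) | Principal investigator and ethics committee decide |
| Discontinuation, worsening criterion | Not met; patient stays |

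The same patient gets three different answers.

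**2. What is lost**

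Depth has two scheduled post-baseline measurements.
- Exit during follow-up loses the 30-day depth.
- Exit during treatment loses the 30-day depth and possibly the end-of-treatment depth. One section ties that scan to the last treatment, which could be early; another ties it to 10 days. If it is not done, baseline is the only depth on file.

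**3. What happens to the patient in the analysis**

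- Informed consent and Discontinuation point to use of the data already recorded.
- Rejection points to removal, because a withdrawn patient has stopped treatment after baseline.

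The text does not say which prevails.

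**4. Size, under assumptions**

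The plan's own figure, 41 per group, is not in dispute. A one-sided pooled test of 87.5% against 62.5%, at alpha 0.05 and 80% power, needs 37 per group, and 37 × 1.10 = 40.7, rounded up to 41. The 10% dropout allowance gives 0.10 × 41 = 4.1, about 4 patients per arm. I use 4 exits for illustration only: the allowance covers all causes and is not an estimate for this trigger.

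*If the last value is carried forward.* Let the true 30-day depth be d cm above the carried value. Each exit makes the arm mean too low by d/41.
- One exit, d = 1: 1/41 = 0.024 cm.
- Four exits, d = 1: 4/41 = 0.098 cm.
- Four exits, d = 3: 12/41 = 0.293 cm.
- Between arms, with exit shares of 10% (cataplasm) and 20% (placebo): (0.20 − 0.10) × d = 0.1 cm for d = 1 and 0.3 cm for d = 3. Reversing the shares reverses the sign; equal shares give zero.

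If patients improve after referral, d is negative and the error in the arm mean changes sign.

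*The same in SD units.* Suppose the 4 deepest of 41 at 30 days carry baseline in one arm and none do in the other. The 4 largest of 41 standard normal values average 1.706 (simulation). With equal SDs, baseline-to-outcome correlation r and a true mean fall D in SD units, the shift in the arm mean is (4/41) × [D − (1 − r) × 1.706]:

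| D | r = 0.3 | r = 0.5 | r = 0.8 |
|---|---|---|---|
| 0 | −0.116 | −0.083 | −0.033 |
| 0.5 | −0.068 | −0.034 | +0.015 |
| 1 | −0.019 | +0.014 | +0.064 |

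Minus means that the arm looks better than it is.

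*If the same four are rejected.* The mean of the remaining 37 is too low by 4 × 1.706/37 = 0.184 SD.

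Both SD calculations put all exits in one arm and choose its deepest patients, so they are extreme cases.

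**The case against.** The sentence stands under Adverse events, in a paragraph that opens with events during the intervention period. It may be meant only for symptoms of an adverse event, such as a skin reaction to the cataplasm. Exit would then follow the severity of the reaction, not ascites depth, and nothing in that section links it to the symptom score. This is a fair reading and limits how firmly the loss can be tied to the outcome. It does not remove the conflict: the wording covers any symptom, and even for adverse-event symptoms it overrides the decision that the sentence before it requires.

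A reader might infer that an earlier depth, perhaps baseline, will definitely replace the 30-day value. The documents do not support that. The last-data rule belongs to patients discontinued under the Discontinuation section, and inclusion of those data is not stated to mean substitution at 30 days. A reader might equally infer that no one is deleted, because recorded data are kept; the Rejection criterion stands against that.

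It is also fair that missing-data methods belong in an analysis plan and that an article condenses operational detail. But the point concerns a stated rule on when measurement ends, and no analysis plan can undo it. Finally, the illustrated effects are small and, under carry-forward, take either sign. That stands.

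**Conclusion.** The concern holds as a conflict between stated rules with a credible route to outcome-related loss of the primary measurement. That the rule conflicts with the Discontinuation threshold and with its preceding sentence is clear from the text. That worsening patients lose the 30-day depth, and possibly the end-of-treatment depth, follows if sites apply the sentence literally.

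The size and direction of any bias are unknown. The illustrations rest on assumed exits, depths and correlations: 0.10 to 0.29 cm in one arm's mean for four exits carried forward; −0.12 to +0.06 SD in the one-arm extreme under carry-forward; 0.18 SD too low if those patients are rejected. Similar exits in both arms would largely cancel.

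A reader might conclude that the rule favours the cataplasm. The documents do not support this: allocation is blinded and the rule is the same in both arms, so any imbalance would come from which arm worsens more often, and that is not known. The point merits correction but does not by itself invalidate the comparison.

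**What to change.** Three aligned changes are needed; rewording Adverse events alone would leave a patient who stops the cataplasm discontinued or rejected under other sections.

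1. **Adverse events, last sentence.** Say that if symptoms aggravate, the cataplasm is stopped and the patient is referred for treatment; whether the patient leaves the trial is decided as the preceding sentence describes.
2. **Rejection, Discontinuation and Dropout.** State that stopping treatment ends treatment only. Ascites depth and the other outcomes are still assessed at the scheduled end-of-treatment and 30-day times unless the patient withdraws consent.
3. **Rejection.** Delete the criterion on stopping treatment after baseline, so that these patients stay in the intention-to-treat analysis.

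Referral, the safety grounds for stopping the cataplasm and reporting to the ethics committee stay as they are.

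The cost is an amendment approved by the Institutional Review Board and a memo to the three sites; no visit is added. Some referred patients may be hard to bring back for the 30-day ultrasound. Trial status reports 78 of 82 patients enrolled, leaving 82 − 78 = 4 to recruit, so the change in conduct helps mainly those patients and any still in follow-up. Deleting the rejection criterion concerns who is analysed and can cover everyone randomised.
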